## Abstract

Improvements in ischemic heart disease (IHD) management have been unbalanced between sexes, with coronary microvascular dysfunction considered the likely underlying reason. The Endocrine Vascular disease Approach (EVA) is an observational study (Clinicaltrial.gov NCT02737982) aiming to assess sex and gender interactions between coronary circulation, sexual hormones, and platelet function. Consecutive patients with IHD undergoing coronary angiography will be recruited: (1) to assess sex and gender differences in angiographic reperfusion indexes; (2) to evaluate the effects of estrogen/androgen on sex-related differences in myocardial ischemia; (3) to investigate the platelet biology differences between men and women with IHD; (4) to verify sex- and gender-driven interplay between response to percutaneous coronary intervention, platelets, sex hormones, and myocardial damage at baseline and its impact on 12-month outcomes. The integration of sex and gender in this translational project on IHD will contribute to the identification of new targets for further innovative clinical interventions.

## Rationale

### Integration of Sex- and Gender-Based Approaches in Cardiovascular Research: The Case of Ischemic Heart Disease

Even though the individual’s sex is among the most important modulators of cardiovascular disease (CVD) risk and response to treatment, the integration of sex in research and clinical decision-making is yet overlooked [1–3]. In the era of precision medicine, reporting on sex- and gender-related variables in clinical trials has become necessary in order to understand how they interact and influence cardiovascular health [1–3]. However, some issues stem from the terminology biases among published literature: while the term “sex” should be used when reporting biological aspects, the term “gender” is more appropriate when reporting gender identity and psychosocial/cultural factors [1].

Ischemic heart disease (IHD) is the main cause of death among women and men [4]. Nonetheless, IHD has been perceived as a primarily “male disease”, and “evidence-based” clinical standards have been based on male pathophysiology and outcomes in basic and clinical research [5]. The low participation of women in clinical trials for CVD is cause of concern, especially in IHD patients [6, 7]. In fact, despite the decrease in CVD mortality over the past decade, trends are less favorable in women [8]. Several studies report clear sex discrepancies in clinical outcomes for IHD patients treated either with conservative or invasive approach (i.e., percutaneous coronary intervention (PCI)) [5, 7]. For example, in acute coronary syndrome (ACS), the benefits of early invasive strategy resulted less effective in women with high-risk profiles [9, 10], exhibiting a higher unadjusted in-hospital mortality in women undergoing PCI [9, 10]. So far, only two studies, the “Variation in Recovery: Role of Gender on Outcomes of Young AMI Patients” [11] and “GENdEr and Sex determInantS of cardiovascular disease: From bench to beyond-Premature Acute Coronary Syndrome” [12, 13], have explored the multilevel interactions between sex and gender in influencing CVD development and management in young patients with ACS [14].

### Beyond Epicardial Obstructive Coronary Artery Disease, Microvascular Dysfunction, and its Assessment

Microvascular perfusion impairment, not explained by an epicardial critical stenosis, is a common finding in IHD and it appears to provide an adjunctive prognostic value in IHD patients [15, 16]. Therefore, the term coronary microvascular dysfunction (CMD) was coined to provide an overarching definition that encompasses different clinical scenarios. The conundrum of CMD ranges from a reduced coronary flow reserve not explained by a flow-limiting epicardial stenosis to the coronary microvascular impairment coexisting with coronary artery disease (CAD). Specifically, CMD can be detected in IHD patients with obstructive CAD undergoing urgent (reperfusion CMD) or elective PCI (interventional CMD), as well as in cases of ischemia and no obstructive CAD (INOCA) [17]. CMD can only be indirectly assessed using invasive and noninvasive techniques that measure parameters strongly dependent on the functional and structural integrity of coronary microcirculation [18]. In the coronary catheterization laboratory, CMD is commonly diagnosed by evaluating coronary blood flow before and after administration of adenosine with a Doppler-tipped guide wire in the coronary artery [19]. However, the corrected thrombolysis in myocardial infarction (TIMI) frame count (cTFC) and myocardial blush grade (MBG) provide easy and accessible angiographic indexes of coronary blood flow that do not require additional coronary artery instrumentation [20]. The intra- and inter-observer reproducibility of cTFC and MBG is acceptable, and dye injection rate and catheter size do not affect its measurement [21, 22]. It is noteworthy that cTFC and MBG have been shown to correlate with other invasive and non-invasive measures of coronary blood flow [23–26]. The cTFC, used as a surrogate marker of coronary blood velocity, predicts coronary microvascular status [27]. Interestingly, abnormal cTFC and MBG have also been related to worse prognosis, although mostly in patients with ACS [28–30]. No association between cTFC and major adverse cardiovascular events (MACE) except angina hospitalization was reported in a pilot study of Women’s Ischemia Syndrome evaluation considering 298 patients with INOCA (defined as no stenosis ≥ 50% in any epicardial vessel), but the study population included only women [31]. Therefore, it remains unclear whether the prognostic implications of an abnormal cTFC or MBG vary in different categories of male and female patients with IHD-for example, in patients varying in clinical presentation, coronary anatomy, or type/extension of coronary lesions.

Preliminary data suggest that cardiac magnetic resonance (CMR) can identify a specific CMD pattern in IHD women [32], suggesting its potential role for recognizing sex-related differences in the conundrum of IHD [33]. This is raising interest in the potential use of CMR, especially to target women with atypical chest pain and to detect the extent of procedural CMD [18, 34, 35]. Over 100 women with CMD, diagnosed by invasive coronary reactivity testing, have showed reduced myocardial perfusion reserve index with vasodilator stress first-pass perfusion CMR compared with an age-matched reference group (*N* = 21). Moreover, the presence of diffuse myocardial fibrosis, documented by native myocardial T1 values assessed by CMR, has been reported in 14 women with CMD without obstructive CAD [32]. However, these data were collected in a female-only population and they lack the comparison with a matched male group.

### Mechanisms Responsible for Microvascular Dysfunction in Ischemic Heart Disease Patients: A Landscape to Explore Under the Lens of Sex

Microvascular impairment seen in diagnostic angiography and after PCI may be responsible for different degrees of myocardial injury and may represent an in vivo human model of ischemia–reperfusion myocardial damage [36]. The impairment of coronary flow owing to functional (i.e., impaired dilation or increased constriction of coronary microvessels) and/or structural abnormalities of the microcirculation can be sustained by several mechanisms [37, 38]. Recently, it has been proposed that CMD in women plays a central role in the genesis of symptoms and myocardial ischemia, specifically in the case of INOCA. Women more frequently experienced persistent ischemic symptoms, regardless of revascularization procedures, as compared to men. Therefore, CMD should be investigated in order to elucidate sex differences in clinical outcomes of IHD patients [39, 40].

Notably, a sex-specific response to myocardial ischemia has been demonstrated in pre-clinical studies [41]. It is unclear which factors contribute to sexual dimorphism in IHD; nevertheless, sex hormones with their multiple cardiovascular effects could play a crucial role [42], especially considering that the estrogen/androgen balance is involved in the cardioprotective response to ischemia–reperfusion injury [43].

In experimental models, females are at lower risk of ischemia–reperfusion damage and estradiol (E2) administered acutely to males can reduce the infarct size [44–46]. Indeed, the estrogen receptor (ER) beta versus ER-alpha receptor-mediated responses and the relative importance of genomic versus non-genomic effects are the subjects of considerable debate [43, 47]. The cardioprotective role of E2 in the modulation of ischemia–reperfusion injury has been extensively investigated: in models, E2 acts at multiple cellular levels during ischemia–reperfusion, including cardiomyocytes and fibroblasts [46, 48–51].

Despite plausible pathological pathways linking endogenous sex hormones and cardiovascular disease, prospective clinical studies have been contradictory. The imbalance between testosterone and E2 was looked at as a potential mechanism of ischemia and CAD development [52–55]. Recently, in postmenopausal women participating in the MESA (Multi-Ethnic Study of Atherosclerosis), a higher testosterone/E2 ratio was shown to be associated with the development of IHD and heart failure events, whereas higher levels of E2 are associated with a reduced risk of ischemic events [56]. Moreover, low levels of serum anti-inflammatory biomarkers are positively associated with sex hormones in male CAD patients [57] suggesting that the imbalance between sex hormones can influence the development of CAD.

### Platelets: Evidence Suggesting Sex Differences Sheds Light on the Potential Role of Hormone Balance

Sex hormones operate at the cellular level, including vascular cells and activated cells recruited at the site of the athero-thombotic process, primarily platelets [58]. Sex differences in platelet reactivity have been reported in response to agonists, regardless of any ongoing anti-platelet therapy [59].

Ex vivo evidence showed that platelets from women without CAD are more reactive than those of men in response to standard concentrations of agonist [60–62], with a greater expression (50–80% higher compared to men) of glycoprotein (GP) IIb/IIIa receptors. Among patients, platelets from women, and in particular Caucasian women, bound more fibrinogen in response to low and high concentrations of ADP and showed more spontaneous aggregation compared to men after adjustment for multiple cardiovascular risk factors [63].

Mechanisms responsible for differences in platelet function are largely unknown. Estrogen and androgen receptors are expressed in platelets [58]; therefore, platelets are an excellent model for studying the non-genomic effects of hormones [64]. Specifically, human platelets have been shown to express only ER-beta and androgen receptors (AR). The effects of E2 and of other forms of estrogen, as well as those of testosterone, have been only partially explored and with conflicting results. Ex vivo acute treatment of platelets with estrone or estriol was shown to increase aggregation in response to common agonists [65]. Conversely, 3-month replacement therapy with estrogen induced a decrease in agonist-induced platelet aggregation in treated patients compared to control groups [66]. Accordingly, chronic treatment with high levels of E2 in experimental models (i.e., mice) produced a significant reduction in platelet responsiveness both ex vivo and in vivo, with a simultaneous increase of bleeding time and resistance to thromboembolism [67].

Concerning the role of AR in the biology of platelet function, rat models have showed that the ex vivo aggregation of platelets isolated from males was greater than that exhibited by those isolated from females and correlates with higher levels of androgens [60]. Consistently, platelet aggregation is reduced following castration in male rats and restored by testosterone administration [68]. The acute treatment of both rat and human platelet-rich plasma with testosterone amplified the aggregation induced by common agonists, indicating its rapid non-genomic responses [69].

Platelets also play a key role in athero-thrombotic mechanisms. Therefore, exploring the effect of sex hormones on platelet function in IHD is a step forward toward a better characterization of biological differences in IHD between men and women.

### EVA Research Hypothesis and Aims

The research hypothesis is that women with IHD have a higher proportion of CMD due to a higher release of platelet-derived vasoconstrictor molecules such as thromboxanes, despite anti-platelet therapy. This status of hyper-activation might be modulated differentially by sex hormone balance among sexes according to age (Fig. 1). Further evidence on platelet biology and sex hormone interplay will provide mechanistic insights to understand CMD. Platelet activation markers will potentially be used as breakthrough innovative biomarkers to better predict outcomes of IHD patients.

**Fig. 1 Fig1:**
[figure not shown]
The EVA hypothesis: platelets, coronary microvascular dysfunction, and unbalanced clinical outcomes in women and men with ischemic heart disease

We plan to conduct an observational study on patients affected by IHD undergoing angiography and/or PCI. Main objectives of EVA are:To assess the sex–gender differences in severity of microvascular reperfusion damage in patients with IHD;To evaluate estrogen/androgen effects on sex-related differences in myocardial ischemia–reperfusion damage occurring during PCI;To investigate the differences in terms of platelet function between men and women affected by IHD and matched by age and clinical characteristics, according to CMD and CAD type;To verify sex- and gender-driven interplay between the response to PCI procedure, platelet function, sex hormones, reperfusion imaging, and myocardial damage severity at baseline and its impact on outcomes at 12-month follow-up.

## Methods

### Study Design and Population

The “Endocrine Vascular disease Approach” (EVA) project (ClinicalTrials.gov identifier NCT02737982) was planned as an observational cohort prospective study. The flow chart of the study and the description of variables that will be considered are summarized in Table 1.

**Table 1 Tab1:**
[figure not shown]
EVA Study design

A registry will be built up of men and women aged 18 and older with suspected IHD who were referred to the catheterization laboratory in order to undergo coronary angiography and/or PCI. Patients will be recruited according to the eligibility criteria reported in Table 2. Therefore, the EVA study population will include patients with stable CAD, patients with non-ST elevation (NSTE) ACS, and patients with ST elevation myocardial infarction (STEMI).

**Table 2 Tab2:** EVA study population eligibility criteria

Inclusion criteria	Exclusion criteria
▪ Patients with ischemic heart disease (acute or chronic) undergoing percutaneous coronary intervention (urgent or elective) ▪ Written informed consent ▪ Both sexes ▪ Aged more than 18 years	▪ Life expectancy less than 12 months ▪ Active cancer (i.e., chemotherapy or ≤ 5 years from diagnosis) ▪ Pregnancy ▪ Previous coronary artery bypass graft ▪ Documented moderate–severe valvular heart disease ▪ Biological or mechanical valves

The study will be conducted in full conformance with the principles of the Declaration of Helsinki, the laws and regulations of Italy, or whichever affords the greater protection to the individual. The study has obtained the required authorization by the local Ethics Committee of Policlinico Umberto I, Sapienza University of Rome (reference 3786, 24/09/2015). Written informed consent will be obtained from all patients.

Among the study population, we will select (1) patients undergoing urgent PCI, specifically subjects who presented within 12 h of the onset of chest pain, who had ST segment elevation of more than 0.1 mV in two contiguous leads, and for whom the clinical decision was made to treat with PCI (STEMI); (2) patients with NSTE ACS defined by acute chest pain but no persistent ST segment elevation. ECG changes may include transient ST segment elevation, persistent or transient ST segment depression, T-wave inversion, flat T waves, or pseudo-normalization of T waves or the ECG may be normal. Myocardial ischemia can occur with (myocardial infarction–NSTEMI) or without cell loss (unstable angina); (3) patients undergoing coronary angiography and elective PCI for stable angina, with stress test inducible myocardial ischemia and de novo native coronary lesion with a stenosis of less 50% (no obstructive CAD) or > 50% stenosis in any epicardial artery (mono-vessel obstructive CAD). Patients will be treated according to standard guidelines based on the CAD type, either with PCI or coronary artery bypass graft.

The recruitment phase started in April 2016 and, currently, 200 patients have already been included in the study.

### Clinical, Pharmacological, and Gender-Related Factors

We will record complete information regarding (1) anthropometric data including height, weight, blood pressure, and heart rate; (2) socioeconomic status and gender-related factors: marital status, education level, income, physical activity (self-administered questionnaire), independent functional status Duke Activity Status Index [70], alcohol intake, smoking habits, perceived stress at work and at home, personality traits, and psychosocial characteristics and support [12, 71]; (3) cardiovascular risk factors (including familiar history of cardiovascular disease; hypertension; dyslipidemia, diabetes, previous cardiovascular events including previous MI and prior stent implantation); (4) symptom evaluation through standardized questionnaires [72, 73]; (5) dietary habits [74]; and (6) pharmacological therapy and Morisky Medication Adherence Scale—4 Items [75].

### Coronary Angiography Assessment

Coronary angiography will be performed according to standard methods. Qualitative and quantitative coronary angiographic analyses will be conducted by a core laboratory blinded to patient data. Time of procedure and timing to access at the catheterization after the first medical contact will be collected to explore chronobiology aspects.

#### Corrected TIMI Frame Count and Myocardial Blush Grade

The analysis of coronary flow will be done according to the TIMI frame count method by Gibson et al. [20, 28]. Values above the normal frame count will be considered suggestive of microcirculatory impairment. The mean TFC for each participant will be calculated using the cTFC of left anterior descending, left circumflex, and right coronary arteries. All participants with a TFC greater than two standard deviations from the normal published range in at least one of the three epicardial coronary arteries will be accepted as having micro-coronary slow flow, while those whose TFC falls within two standard deviations of the published normal range will be considered as having normal coronary flow.

The MBG [29] will be used to assess the filling and clearance of contrast in the myocardium. A rest or post-PCI MBG of less than 2 will define an impairment of coronary microcirculation [76].

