### Statistical Analysis Plan

The data will be analyzed by appropriate statistics. Student’s *t* test and Pearson correlation will be used for normally distributed variables. When necessary, log transformation will be used to normalize the data, or appropriate non-parametric tests will be employed (Mann–Whitney *U* test and Spearman rank correlation test). Adjusted multivariate analyses will be used to assess the differences and relationships between angiographic, laboratory, and clinical characteristics, stratifying the analysis on sex- and gender-related variables. Among the pre-specified subgroup analyses, we will explore the clinical presentation of ischemia (stable vs. acute coronary syndrome), the type of disease (obstructive vs. non-obstructive disease), traditional cardiovascular risk factors, medication adherence, and the gender construct including gender identity, gender role, gender relations, and institutionalized gender. We will consider the interaction term between sex and hormones in the changes of platelet biomarkers and angiographic index of coronary flow.

All calculations will be made using appropriate statistical software packages.

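### The frame count is summarised only across all three coronary arteries, never for the PCI-treated artery on its own, so untreated arteries are mixed into the PCI reperfusion question

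*Protocol article*

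**What the plan says.** The protocol article, section Corrected TIMI Frame Count and Myocardial Blush Grade, fixes two patient-level summaries of the frame count.

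- A continuous one: "The mean TFC for each participant will be calculated using the cTFC of left anterior descending, left circumflex, and right coronary arteries".
- A binary one: a patient whose count lies more than two standard deviations from the published normal range "in at least one of the three epicardial coronary arteries will be accepted as having micro-coronary slow flow".

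The article defines no count for the treated, target or culprit artery. It does not say whether frame counts are read before PCI, after it, or both.

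The objectives, under EVA Research Hypothesis and Aims, are:

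- Objective 1: "To assess the sex–gender differences in severity of microvascular reperfusion damage in patients with IHD".
- Objective 2: "To evaluate estrogen/androgen effects on sex-related differences in myocardial ischemia–reperfusion damage occurring during PCI".

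The abstract names angiographic reperfusion indexes as the measure for the first aim. The Statistical Analysis Plan section adds: "We will consider the interaction term between sex and hormones in the changes of platelet biomarkers and angiographic index of coronary flow".

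The stable stratum in Study Design and Population includes patients with "> 50% stenosis in any epicardial artery (mono-vessel obstructive CAD". The section on extension and localization of CAD plans one-, two- and three-vessel groups.

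**The concern.** PCI reperfuses the artery it treats, so damage occurring during PCI is a question about that artery's territory. In a one-vessel procedure the three-artery mean gives two thirds of its weight to arteries that PCI did not touch. The any-artery label can be set by an untreated artery alone. Choosing one of the two summaries over the other does not help, because neither isolates the treated territory.

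Two errors are possible, and they run in opposite directions:

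- **Dilution.** A sex or hormone effect confined to the treated artery is reduced by arteries that do not carry it.
- **Contamination.** The study's own hypothesis is that women have more coronary microvascular dysfunction. If untreated arteries show it, the summary can give a sex difference that is not PCI damage.

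At stake is whether a null or a positive frame-count result in PCI patients can be attributed to reperfusion.

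**Working it through.** **1. The plan's own figure.** The sample size is built on MBG < 2, at 50% in women and 30% in men, with alpha 5% (taken as two-sided) and power 80%. With pooled variance and no continuity correction:

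n = [1.96·√(2·0.4·0.6) + 0.8416·√(0.5·0.5 + 0.3·0.7)]² / 0.2² = (1.358 + 0.571)² / 0.04 ≈ 93 per group, or 186 in total.

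For 10% drop-out, 93/0.9 gives 104 per group (208), close to the stated 210. The figure reproduces and does not involve the frame count.

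**2. Inputs for the frame count.** The documents give no frame-count SD, abnormal rate or between-artery correlation r. All of these are assumptions below. The benchmark is the treated-artery effect that has 80% power with 93 per sex: d = (1.96 + 0.8416)·√(2/93) = 0.411 SD.

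**3. Three-artery mean, one treated artery, effect only there, equal SDs.** The effect on the mean is d/3. The SD of the mean is √((1+2r)/3). The standardised effect is therefore multiplied by (1/3)/√((1+2r)/3), and the equivalent sample-size inflation is 3(1+2r).

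| r | multiplier | effect (SD) | power, 93 per sex | inflation |
|---|---|---|---|---|
| 0 | 0.577 | 0.237 | 37% | 3.0 |
| 0.3 | 0.456 | 0.188 | 25% | 4.8 |
| 0.5 | 0.408 | 0.168 | 21% | 6.0 |
| 0.8 | 0.358 | 0.147 | 17% | 7.8 |

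**4. Three-artery mean under other assumptions.**

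- Effect in one treated artery, untreated SD half the treated SD, r = 0: SD of the mean = √(1 + 0.25 + 0.25)/3 = 0.408. The multiplier is 0.333/0.408 = 0.82 and power is about 63%.
- Effect shared by all three arteries, equal SDs, r = 0.5: the effect on the mean stays d and its SD is 0.816. The multiplier is 1/0.816 = 1.22 and power is about 93%, better than a single artery.

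**5. Any-artery label, dilution.** Suppose treated-artery positivity is 50% against 30%, and each untreated artery is positive with probability q, independently and equally in both sexes. The patient-level rate is 1 − (1−p)(1−q)², where p is the treated-artery rate.

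| q | women | men | difference (points) | power, 93 per sex |
|---|---|---|---|---|
| 0 | 50.0% | 30.0% | 20.0 | 80% |
| 2.3% | 52.3% | 33.2% | 19.1 | 75% |
| 10% | 59.5% | 43.3% | 16.2 | 60% |
| 20% | 68.0% | 55.2% | 12.8 | 43% |

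**6. Any-artery label, contamination.** Suppose there is no treated-artery difference (30% in both sexes), with q = 20% in women and 10% in men. The label then gives 1 − 0.7·0.8² = 55% against 1 − 0.7·0.9² = 43%. That is a 12-point sex difference with no difference in PCI damage.

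**The case against.** The strongest case on the other side has five parts.

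- **The treated artery is measured.** A reader might infer that the plan ignores it. It does not: the treated artery is normally one of the three. The fault is only that it is never analysed on its own.
- **Objective 1 is not confined to PCI.** It speaks of patients with IHD. The Methods text admits patients having angiography and/or PCI, including those without obstructive disease, although the inclusion line of Table 2 names only PCI. Where no artery is treated, a three-artery summary is sensible. It would be wrong to call it the wrong territory for objective 1 as a whole. This stands and limits the point to objective 2 and the PCI patients within objective 1.
- **The large power losses are conditional.** A reader might take the 3- to 8-fold loss of effective sample size as the expected cost. It requires one-vessel PCI, an effect confined to the treated artery and equal SDs. The mono-vessel wording covers only the stable stratum, and two- and three-vessel groups are planned. Platelet-derived vasoconstrictors and hormones need not act in one artery only, and under a shared effect the mean gains power. This stands.
- **A null sex-by-hormone result is not shown to be likely.** The calculation is a cross-sectional main effect, whereas the plan's model concerns an interaction and changes. If change means before to after PCI, and untreated arteries add little change and little variance, then effect and SD both shrink to about one third and the standardised effect is largely kept. This stands.
- **The detail may sit in a fuller document.** The article does not assign either cTFC summary to a named objective. That does not dispose of the point: the article states both derivations, and both span all three arteries.

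**Conclusion.** The point holds in limited form. Both stated frame-count summaries mix untreated arteries into a question about PCI damage. This affects objective 2 and the PCI patients within objective 1.

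Neither the size nor the direction of the effect can be derived from the documents. With 93 per sex and a treated-artery effect that has 80% power, power on the three-artery mean runs from 17%–37% (effect in one treated artery, equal SDs, r from 0.8 to 0), through about 63% (untreated SD half the treated SD, r = 0), to about 93% (effect shared by all arteries, r = 0.5). The any-artery label can dilute a real difference or produce one that is not due to PCI.

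MBG is the only powered index, and the totals of 186 and 210 are untouched. This is a worthwhile correction to an index without its own power calculation, not a threat to the study's sample size.

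**What to change.** For PCI patients, define the frame-count index for objective 2 and for the PCI part of objective 1 as the post-PCI cTFC of the treated artery, or of the culprit artery if several are treated. Use the same artery's pre-PCI value where it was recorded and is countable; an occluded artery will have none.

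Keep the three-artery mean and the any-artery label as global flow measures and for patients without PCI. Report the two kinds of index separately rather than pooling them in one sex contrast.

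The cost is mainly wording. The three-artery mean already needs a count for each artery, and a blinded core laboratory does the angiographic analysis. The article does not say that counts are read both before and after PCI, so the pre-PCI value may need extra reading. There are two small downsides: two cTFC summaries are reported instead of one, and the PCI-only contrast has fewer patients than the whole cohort.

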#### Sample Size Calculation

Preliminary data reported a higher rate of pathologic post-procedural MBG in women (50%) compared to men (30%) despite a TIMI flow grade 3 after PCI [80].

Therefore, the study requires 186 patients (93 per group, ratio men/women 1:1) to detect a difference of 20% in MBG < 2 at baseline and after PCI between men and women, with an alpha error equal to 5% and a power of 80%. Considering a drop-out rate of around 10%, total sample size required is 210 (105 per group).

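### The rules for microvascular impairment (MBG<2, slow cTFC) carry no stenosis or timing condition, so flow limited by an epicardial lesion can be labelled as coronary microvascular dysfunction at baseline

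*Protocol article*

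**What the plan says.** Two rules appear in the section on corrected TIMI frame count and myocardial blush grade.

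- **Blush grade:** "A rest or post-PCI MBG of less than 2 will define an impairment of coronary microcirculation".
- **Frame count:** a patient whose count is "greater than two standard deviations from the normal published range in at least one of the three epicardial coronary arteries" is classed as having micro-coronary slow flow. The section introduces this with "Values above the normal frame count will be considered suggestive of microcirculatory impairment".

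Neither rule refers to the degree of stenosis. The frame-count rule does not say whether it is read before or after PCI.

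The rationale section on microvascular dysfunction introduces the concept differently: "Microvascular perfusion impairment, not explained by an epicardial critical stenosis, is a common finding in IHD". It adds that "CMD can be detected in IHD patients with obstructive CAD undergoing urgent (reperfusion CMD) or elective PCI (interventional CMD"), which ties the label in obstructive disease to the PCI setting.

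Study Design and Population admits stable CAD, NSTE ACS and STEMI. The section on extension and localization of CAD classifies patients as obstructive (stenosis of 50% or more) or not, and by number of diseased vessels.

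Sample Size Calculation powers a 20-point difference in MBG<2 at baseline and after PCI. Its planning rates, 50% in women and 30% in men, are post-procedural and were seen "despite a TIMI flow grade 3 after PCI".

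**The concern.** By the article's own description, MBG grades how contrast fills and clears from the myocardium. Behind a tight or occluded epicardial artery, filling is poor whatever the state of the microvessels, and the frame count in that artery is slow for the same reason. Without a stenosis or timing condition, such a reading satisfies the rule and the patient is labelled as having microvascular impairment.

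Two things are at stake. First, the baseline sex comparison: patients who are positive only because of an epicardial lesion dilute a true difference. If men and women differ in obstructive disease or in STEMI share, they also bias it. Second, the third objective compares platelet function between men and women according to CMD and CAD type, so a mislabelled patient enters the wrong CMD group there too.

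**Working it through.** **1. The plan's own figure.** Inputs from Sample Size Calculation: 50% and 30%, alpha 5% (taken as two-sided), power 80%, ratio 1:1. With mean rate 0.40,

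n per sex = [1.960·√(2·0.40·0.60) + 0.842·√(0.50·0.50 + 0.30·0.70)]² / 0.20² = (1.358 + 0.571)² / 0.04 ≈ 93.

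The stated 93 per sex (186 in total) is reproduced. Allowing for 10% drop-out, 186/0.9 = 207, close to the stated 210. The sample size arithmetic is not at fault.

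**2. Concept and rule side by side.**

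| Element | Rationale and planning data | Classification rules |
|---|---|---|
| Stenosis | "Microvascular perfusion impairment, not explained by an epicardial critical stenosis" | no condition |
| Timing in obstructive disease | tied to PCI; planning rates are post-procedural | MBG: rest or post-PCI; cTFC: not stated |
| Epicardial flow | TIMI 3 after PCI in the planning data | no condition |
| Artery | not specified | cTFC: any of three, diseased artery included |

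The only place where MBG<2 is joined to absence of obstructive disease is the second group of the CMR sub-study (N = 10).

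The gap in the cTFC rule does not depend on how *rest* is read. Even if frame counts were taken only after PCI, an untreated stenosed artery in a patient with two- or three-vessel disease would still count.

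**3. Illustration for the baseline comparison.** Take the planning rates as the true rates p. Let f be the share of patients without CMD who read positive before PCI because of the epicardial lesion. Then

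observed rate = p + (1 − p)·f,

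and, with p̄ the mean of the two observed rates p₁ and p₂ and d their difference,

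power at n = 93 = Φ{ [|d| − 1.960·√(2p̄(1−p̄)/n)] / √[(p₁(1−p₁) + p₂(1−p₂))/n] }.

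**The article gives no value for f; every f below is an assumption.**

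| f women | f men | Observed women | Observed men | Difference (points) | Power at 93 per sex |
|---|---|---|---|---|---|
| 0% | 0% | 50% | 30% | 20 | 80% |
| 10% | 10% | 55% | 37% | 18 | 70% |
| 20% | 20% | 60% | 44% | 16 | 59% |
| 30% | 30% | 65% | 51% | 14 | 49% |
| 10% | 20% | 55% | 44% | 11 | 32% |
| 20% | 30% | 60% | 51% | 9 | 23% |
| 20% | 40% | 60% | 58% | 2 | about 5% |

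The direction reverses when 0.30 + 0.70·f(men) exceeds 0.50 + 0.50·f(women). With f(women) = 10%, this needs f(men) above (0.20 + 0.05)/0.70 = 36%.

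With no true difference (40% in both sexes) and f of 20% in women and 40% in men, the observed rates are 0.40 + 0.60·0.20 = 52% and 0.40 + 0.60·0.40 = 64%. That is a false 12-point excess in men, significant in about 38% of studies.

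None of these figures applies to the post-PCI reading in a treated artery.

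**The case against.** **The wording allows a harmless reading.** *Rest* may mean patients who have angiography without PCI, and *post-PCI* those who are treated. The abstract and objectives also use baseline in contrast to 12 months, not in contrast to after PCI. This stands in part: the article never writes pre-PCI in the rule. A reader might infer that obstruction before PCI is certainly counted as CMD, but the text does not establish that for MBG. On the other hand, the sample size section names baseline and after PCI as separate readings. The study text also provides for bypass surgery as an alternative to PCI, so an untreated patient may still have obstructive disease. And this reading leaves the any-artery cTFC rule as it was.

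**CMD may coexist with CAD.** The rationale says so, and this stands. Obstructive patients need not be excluded. What fails is attributing to the microvessels a reading taken behind a significant stenosis.

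**The main comparison is post-procedural.** The first objective concerns reperfusion damage, and the planning rates are post-PCI. This stands. A reader might infer that the powered comparison as a whole is invalid; only its baseline part is exposed.

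**Adjustment and subgroups deal with it.** The analysis plan section foresees adjusted analyses and subgroups by presentation and by obstructive disease. These reduce confounding between patient types. They do not correct the label of an individual, and the problem persists within the obstructive stratum.

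**Reading rules may be in the full protocol.** Core-laboratory detail may well be there. But the article does not leave the definition open: it states one, and that definition conflicts with its own concept.

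**Frame-count wording.** A reader might also see two competing cTFC thresholds, or an idle three-vessel mean. The two-SD sentence is the operative rule, the earlier sentence is introductory, and a mean can serve as a descriptive measure. Neither is a defect of substance.

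**Conclusion.** The point holds for baseline MBG, on the condition that *rest* or *baseline* includes readings before PCI in PCI patients. It holds for the any-artery cTFC rule without that condition. In both cases the rule as written can label epicardial flow limitation as CMD, and the sex comparison of baseline CMD can partly reflect differences in obstruction or presentation.

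The size cannot be known from the article. Under equal assumed shares of 10% to 30%, baseline power falls from 80% to between 70% and 49%. Unequal shares could shrink the difference further or reverse it. A reader might take the unequal scenarios as an estimate of what will happen. They are not: the article reports no occlusion or obstruction share by sex, and the model assumes that every patient with true CMD reads positive.

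The post-PCI MBG comparison, which matches the planning data, is largely unaffected.

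**What to change.** Change the endpoint definition as follows.

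1. Make post-PCI MBG<2 the endpoint of the powered comparison, in PCI patients.
2. Define CMD from post-PCI MBG and cTFC in the treated artery, and from resting MBG and cTFC only in arteries without obstructive stenosis (50% or more, the article's own cut-off).
3. Report pre-PCI readings in obstructed arteries descriptively, outside the CMD label.
4. Keep patients with less than TIMI 3 flow after PCI in the main result, and show the TIMI 3 subset as a sensitivity analysis. That subset matches the planning data. Making TIMI 3 a condition for classification would remove patients who may have the worst reperfusion damage, which the study sets out to measure.

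**Cost.** The change is one of wording: the blinded core laboratory already analyses the angiograms. Some arteries will have no classifiable pre-PCI value. The number of eligible arteries will differ between patients, so an any-artery rule should state how many were assessed. Only PCI patients then count towards the 93 per sex. The planned 105 per sex leaves 105 − 93 = 12 per sex to cover drop-out and patients without PCI together, so the number of PCI patients should be checked. As 200 patients had already been included, the definition should be fixed before core-laboratory readings are linked to sex.
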